## Background

Parkinson's disease (PD) is the second most common neurodegenerative disorder with a life-time risk of 2 percent in males and 1.3 percent in females [1]. Diagnosis is based on clinical criteria. In most cases the diagnosis of PD is straightforward when cardinal clinical signs and symptoms as bradykinesia, rigidity, and resting tremor are present [2]. However, these main features of PD are shared, at least in part, by atypical parkinsonian syndromes (APS), like multi system atrophy (MSA), progressive supranuclear palsy (PSP) and corticobasal degeneration), essential tremor (ET), vascular parkinsonism (VP), drug induced parkinsonism (DIP), dementia with Lewy bodies and Alzheimer's disease. Besides delineating PD from the above parkinsonian syndromes, distinguishing PD from normality can also be difficult, especially in early stage of the disease [3].

The gold standard for the diagnosis of PD is post-mortem neuropathological examination. Clinicopathological studies show that 2–25 % of the patients with IPD are classified incorrectly in the final stage of their disease, even by specialists in movement disorders, with MSA and PSP accounting for most false positives [2,4,5]. Diagnostic accuracy is certainly less than 90% in earlier disease, as Litvan et al. found that the median sensitivity for the diagnosis of PD increased from 73% at the first visit to 80% to the last visit after a mean follow-up of 9 years, and the median positive predictive value increased from 46 to 64% [6].

A reliable test to diagnose PD is important for two reasons. Prognosis and medical treatment in the various parkinsonian syndromes differ considerably and an objective disease marker would facilitate the development of neuroprotective therapies [7,8]. Several procedures have been proposed to diagnose PD: functional imaging with Positron Emission Tomography (PET)-scan or Single Photon Emission Computer Tomography (SPECT), olfactory- and neuropsychological tests, and DNA tests [9-12].

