At the moment neuro-imaging techniques like PET and SPECT are the most widely used diagnostic tools [8]. PET is at least as reliable as SPECT, but its use in routine clinical practice is limited by high costs and a relative short half-life of its radioactive tracers [13-16]. Despite its widespread use, there is no consensus about the value of SPECT scintigraphy in the differential diagnosis of PD [8,17-19]. The ability of SPECT scanning to discriminate PD from normality and other parkinsonian syndromes varies greatly among different studies. A major issue here is that many studies use well-defined later-stage patients that are obviously not representative for the diagnostic problem that one wants to solve with a SPECT.

A more recent addition to the diagnostic armamentarium of the neurologist is transcranial duplex scanning (TCD) of the substantia nigra (SN) in the brainstem. In 1994 Becker discovered that patients with PD had bilateral hyperechogenicity of the SN [12], probably caused by iron deposition [20,21]. Several publications confirmed this observation that up to 90% of PD patients have increased echo-intensity of the SN. In healthy subjects and in patients with ET or VP this hyperintensity of the SN is only found in 10–25% [20,22-29].

This technique has high inter-observer reliability [22,25,29]. In a pilot study with 45 patients with PD or APS who underwent SPECT and TCD we found a positive predictive value of 95% of an abnormal TCD for an abnormal FP-CIT SPECT scan [30].

Based on this study we hypothesized that TCD of substantia nigra is a tool deserving a place in the diagnostic work-up of PD/Parkinsonism patients. TCD is less costly and less invasive than SPECT [31]. Since a diagnostic test for parkinsonian syndromes is especially valuable in the early stage of disease(s), we devised a prospective diagnostic study with a clinical follow-up after 2 years as surrogate gold standard. As SPECT is currently the most widely used diagnostic tool in parkinsonian syndromes we included this in the study to directly compare the two techniques as to their diagnostic capacities in this field.

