#### Inclusion criteria

1. Patients with parkinsonian signs and symptoms of unclear origin at the time of visit at the Neurology Outpatient Clinic. In his/her differential diagnosis the treating neurologist should be considering one of the following conditions: PD, MSA, and PSP. ET, VP or DIP.

2. Age older than 18 years.

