### Methods

After informed consent all subjects will undergo a structured interview, neurological examination (See Additional file 1), TCD and SPECT within 6 weeks of the initial visit at the Outpatient Clinic. After two years all patients are re-examined by two movement disorder specialist neurologists for a final clinical diagnosis. This diagnosis serves as a surrogate gold standard to calculate the accuracy of SPECT and TCD to differentiate between PD and other types of parkinsonism.

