### Data analysis

Our main hypothesis is that TCD is as sensitive as SPECT to differentiate PD from other parkinsonian disorders. For the power analyses we assumed a sensitivity of SPECT of 90%, based on the analysis of our own data on 248 consecutive patients [19]. Assuming this 90% for TCD sensitivity we can accept as lowest border of the 95% confidence interval, 86% or higher:

*SD *= (√ (p1 (1-p1))/n → p1 = 0.9, sd 0.02, implying n = 190 patients, needed who have the hyperintensity of SN with TCD scanning.

In our pilot study 15% of the patients had an insufficient temporal bone window, so 224 patients are needed to compensate for the amount of inconclusive TCDs [28]. Based on this study we expect that 90% of all patients with inconclusive parkinsonism will ultimately have PD, so we set a target of initial 250 patients with unclear parkinsonism needed for this trial. We will calculate the sensitivity and specificity, positive predictive value, negative predictive value and diagnostic odd's ratio (OR) with its 95% confidence intervals (95% CI) of the first clinical judgment, TCD, FP-CIT SPECT scan and smell tests to predict the clinical diagnosis after 2 year follow-up. Accuracy is determined for all parkinsonian subgroups separately (PD versus APS, PD versus ET, and PD versus VP, PD versus DIP, and PD versus all other types of parkinsonism). For expected SPECT, TCD and smell tests scores for each parkinsonian disorder, see table 1.

**Table 1 T1:** Expected TCE, FP-CIT SPECT and odour recognition results for all parkinsonian disorders

Disease	FP-CIT SPECT abnormal, [19, 46]	abnormal SN TCD [47]	odour recognition deficit	cognition deficit
IPD	++	+++	+++	±
ET	Normal	normal	normal	normal
VP	normal *	normal	normal (?)	±
DIP **	normal (+)	normal (+)	normal (+)	normal (±)
MSA	++	±	+	±
PSP	++	± (?)	normal (±)	++

= normal FP-CIT tracer binding ratios

↓: FP-CIT binding of at least 2 sd. below healthy controls

* especially visual judgement together with CT or MRI

** At least 10% percent of the patients with DIP will develop to the PD [48]. So some patients in early stages of PD can theoretically present as DIP. Berg et al. investigated the relation between echointensity of SN on TCD and DIP after the start of antipsychotic drugs. Patients with serious parkinsonism scored higher echointensity as patients with mild or no parkinsonism [47].

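### None of the listed accuracy contrasts covers a patient whose agreed two-year diagnosis is no parkinsonian disorder; leaving such patients out understates the negative predictive value

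*Protocol article*

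**What the plan says.** The Data analysis section introduces the contrasts with "Accuracy is determined for all parkinsonian subgroups separately" and names five: PD against APS, ET, VP and DIP, "and PD versus all other types of parkinsonism". Two other statements have the same scope. The Methods section says that the two-year diagnosis serves "to calculate the accuracy of SPECT and TCD to differentiate between PD and other types of parkinsonism", and the main hypothesis is that "TCD is as sensitive as SPECT to differentiate PD from other parkinsonian disorders". Table 1 has rows for IPD, ET, VP, DIP, MSA and PSP only.

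The Background draws the diagnostic problem more widely. After listing the parkinsonian syndromes it adds, as a separate difficulty, that "distinguishing PD from normality can also be difficult, especially in early stage of the disease". It makes the same split when it discusses SPECT.

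The first inclusion criterion admits "Patients with parkinsonian signs and symptoms of unclear origin at the time of visit at the Neurology Outpatient Clinic", and also requires the treating neurologist to have PD, MSA, PSP, ET, VP or DIP in the differential diagnosis. The section on re-examination at two years codes a final diagnosis as inconclusive only when the two specialists disagree.

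**The concern.** Being under consideration for one of six disorders at the first visit does not mean having one of them two years later. Patients with a clear diagnosis are excluded, so the cohort is the early, ambiguous group for which the Background raises the question of normality. Two matching diagnoses of no parkinsonian disorder are a settled result, but no named contrast has a place for them.

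If the analyst follows the list, these patients are removed on information that arrives two years after the test. The predictive values then describe a group that the neurologist cannot pick out when ordering the test. This sits badly with the stated purpose, which is accuracy in patients whose syndrome cannot yet be defined, and with the article's own criticism of studies in well-defined patients. The expected non-PD group is small, so each patient left out counts. The same contrasts serve the first clinical judgment, TCD, SPECT and the smell tests, so the gap is common to all four.

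**Working it through.** **Inputs from the protocol article.** The plan gives no expected NPV, PPV or specificity to reproduce. It gives a target of 250 patients, an expected PD share of 90% and an assumed TCD sensitivity of 90% (Data analysis). It also gives a TCD-positive rate outside PD: "In healthy subjects and in patients with ET or VP this hyperintensity of the SN is only found in 10–25" per cent (Background). The last steps to the target do reproduce: 190/0.85 = 223.5, taken as 224, and 224/0.90 = 248.9, taken as 250. The point does not depend on the 190.

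**Assumptions.** Three inputs are not in the documents:
- the number k of non-PD patients with no parkinsonian disorder;
- the false-positive rate in all other non-PD patients together (the Background gives ET and VP the same range as healthy subjects, but no rate for MSA or PSP);
- the rate in patients who had parkinsonian signs and were later judged normal, for whom the healthy-subject range is borrowed.

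**Direction, whatever the rates.** Leaving out non-PD patients does not touch the PD column, so TP and FN are fixed.
- NPV = TN/(TN + FN) falls whenever a true negative is removed.
- PPV = TP/(TP + FP) rises whenever a false positive is removed.
- Specificity = TN/(TN + FP) changes only if the false-positive rate among those left out differs from the rate among those kept.
- Sensitivity = TP/(TP + FN) does not change.

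**Size with equal rates.** PD = 0.90 × 250 = 225; non-PD = 25; TP = 0.90 × 225 = 202.5; FN = 22.5. The false-positive rate is 25% in all non-PD patients, the top of the Background range.

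| Non-PD patients counted | TN | FP | NPV | PPV | Specificity |
|---|---|---|---|---|---|
| All 25 (also the result as written if k = 0) | 18.75 | 6.25 | 18.75/41.25 = 45.5% | 202.5/208.75 = 97.0% | 75% |
| 24 (k = 1 left out) | 18 | 6 | 18/40.5 = 44.4% | 202.5/208.5 = 97.1% | 75% |
| 20 (k = 5 left out) | 15 | 5 | 15/37.5 = 40.0% | 202.5/207.5 = 97.6% | 75% |

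At the bottom of the range (10% in all non-PD patients), NPV with all 25 is 22.5/45 = 50.0%. It is 21.6/44.1 = 49.0% if k = 1 and 18/40.5 = 44.4% if k = 5. With equal rates the diagnostic odds ratio does not move, because neither sensitivity nor specificity does.

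**Size with unequal rates, k = 5.**
- 25% in other non-PD and 10% in no-disorder patients: counting the five moves specificity from 75% to 78%, NPV from 40.0% to 46.4% and PPV from 97.6% to 97.4%.
- 10% in other non-PD and 25% in no-disorder patients: specificity goes from 90% to 87%, NPV from 44.4% to 49.2% and PPV from 99.0% to 98.4%.

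**Wider grid.** With k from 5 to 15 of 25, 10% to 50% in other non-PD patients and 10% or 25% in no-disorder patients, counting them raises NPV by about 5 to 27 points and lowers PPV by 0.2 to 1.8 points. Specificity changes by −9 to +24 points. The upper end needs more than half of the non-PD group to have no disorder, which nothing in the documents suggests.

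**Bone window.** If the 15% inconclusive scans fall evenly, 0.85 × 25 = 21.25 non-PD patients remain and the percentages above do not change.

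**The case against.** The best defence has four parts.

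- **Eligibility is narrower than its first sentence suggests.** The neurologist must be considering one of six named disorders, and each of them is PD or is covered by a contrast. This stands. A reader might infer that unclear signs at one visit are enough, and the criterion does not support that. It narrows entry, but it does not rule out a final diagnosis of no disorder.
- **The article uses parkinsonism broadly.** ET is counted in, and the Background lists Alzheimer's disease and dementia with Lewy bodies among the parkinsonian syndromes. This stands. A reader might infer that a final diagnosis of Alzheimer's disease also falls outside every contrast, but in the article's own vocabulary it belongs to the last one. The gap is limited to patients judged normal, whom the Background sets apart.
- **Nothing says that these patients are dropped.** The sentence before the list promises accuracy measures against the two-year diagnosis without restricting it, and the list can be read as a breakdown. This stands in part: exclusion is what follows from the list, not a stated rule. But the general sentence does not define a comparison of PD with all non-PD, while the aim and the hypothesis share the narrower scope.
- **Coding a rare final diagnosis is a detail for the full protocol or analysis plan.** This would carry weight if the article were silent. It is not silent: it names the comparison groups, and the set is too narrow for the population enrolled.

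The size is also open to attack. No number of such patients is given, a number near zero has no effect, and the 10–25% range comes from healthy subjects. All of that is accepted and is why the result is shown from k = 0 upwards.

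**Conclusion.** The point holds, in a limited form. The listed contrasts and the stated aim stop at types of parkinsonism, while the Background and the eligibility criteria allow for an agreed diagnosis of no parkinsonian disorder. Following the list selects patients on a two-year outcome. The consequences that are certain in direction are an understated NPV, a slightly overstated PPV and a smaller non-PD denominator.

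The size depends on a number that the documents do not give. With equal 25% false-positive rates, the NPV as written falls short by nothing if k = 0, by about 1 point if k = 1 and by about 5.5 points if k = 5.

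A reader might infer that all the accuracy measures are distorted. The documents do not support this. PPV moves by under 2 points across the grid. Specificity has no fixed direction and does not move if the false-positive rates are equal, which is the only pattern the Background's single range for healthy subjects, ET and VP suggests. Sensitivity, which carries the main hypothesis and the sample size, is unaffected.

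**What to change.** In Data analysis, add as the overall contrast for specificity, PPV, NPV and the diagnostic odds ratio: *PD versus every other agreed final diagnosis, including no parkinsonian disorder*. Keep the five listed contrasts, including the one against all other types of parkinsonism, as subgroup contrasts. Align the sentence on the aim in the Methods section.

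The cost is two sentences. No extra patients, tests or follow-up are needed, since these patients are scanned and re-examined anyway. Making the change before the two-year diagnoses are known also prevents a choice of denominator that depends on the results.

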*** In our retrospective trial 76% of the 27 patients with APS had FP-CIT binding lower as 2 standard deviations below healthy controls. In the 11 studies included in our meta-analysis this percentage varies form 67 to 100% [19, 46]

Additionally we will determine the predictive value of TCD compatible with PD for an abnormal FP-CIT SPECT scan. Finally the inter-observer reliability for SN and RN judgement by TCD will be determined (Cohen's kappa test).

SPSS 11.0 for windows (SPSS, Chicago, IL, USA) and StataSE9 (Stata corporation, Texas, USA) will be used for statistical analysis.

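### The additional TCD-SPECT analysis reports only the predictive value of a PD-type TCD, which on the planning figures barely separates an informative TCD from an uninformative one

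*Protocol article*

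**What the plan says.** The Data analysis section of the protocol article first sets out the main analysis. The first clinical judgment, TCD, SPECT and smell tests are each compared with the two-year clinical diagnosis by sensitivity, specificity, both predictive values and the diagnostic odds ratio, with 95% confidence intervals, overall and for PD against each other group. After Table 1 it adds a separate analysis that links the two imaging tests directly: "Additionally we will determine the predictive value of TCD compatible with PD for an abnormal FP-CIT SPECT scan". No other measure is named for that link.

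The same measure appears in the Background for the pilot of 45 patients with PD or atypical parkinsonism (APS): "we found a positive predictive value of 95% of an abnormal TCD for an abnormal FP-CIT SPECT scan". The study hypothesis is said to rest on that pilot. Neither its 2x2 counts nor its overall rate of abnormal SPECT is given.

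The planning figures that bear on this measure also stand in Data analysis. On case mix: "we expect that 90% of all patients with inconclusive parkinsonism will ultimately have PD". On SPECT in PD: "For the power analyses we assumed a sensitivity of SPECT of 90" per cent. On SPECT in APS, in the notes to Table 1: "76% of the 27 patients with APS had FP-CIT binding lower as 2 standard deviations below healthy controls", and "In the 11 studies included in our meta-analysis this percentage varies form 67 to 100" per cent. Table 1 ("Expected TCE, FP-CIT SPECT and odour recognition results for all parkinsonian disorders") expects SPECT to be as abnormal in MSA and PSP as in PD, and normal or mostly normal in essential tremor, vascular and drug-induced parkinsonism. It expects TCD to be clearly abnormal in PD and only equivocal in MSA and PSP.

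**The concern.** A positive predictive value looks only at TCD-positive patients. If TCD carried no information about SPECT, the value would equal the overall proportion of abnormal scans. Where that proportion is high, the value is high for any TCD. The half of the table that would reveal this, the SPECT result in patients with a normal TCD, is not part of the stated measure.

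Two features add to this. The pilot figure comes from PD and APS patients, two groups in which the protocol expects SPECT to be mostly abnormal, and it is given without a base rate. And a PD-type TCD in an MSA or PSP patient with an abnormal SPECT counts as a success here, although it is an error for telling PD from other parkinsonism.

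The Background argues that TCD is cheaper and less invasive than SPECT and deserves a place in the work-up. A value of 85% to 90% from this analysis could be read as broadly confirming the pilot, when the case mix alone would produce it.

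**Working it through.** **Pilot figure.** The 95% cannot be reproduced, because the counts are not given. If between 15 and 45 patients were TCD-positive, the fractions that round to 95% run from 18/19 to 42/44. Their exact lower 95% limits run from 74% to 85%.

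**Inputs.**
- PD share 90%, SPECT sensitivity in PD 90%, inconclusive TCD 15%, target 250 patients (Data analysis).
- SPECT abnormal in APS: 76%, range 67% to 100% (notes to Table 1).
- x = proportion of non-PD patients with an abnormal SPECT. The protocol does not give the mix of non-PD diagnoses, so x is varied.

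**Formulas.**
- TCD unrelated to SPECT: predictive value = overall proportion abnormal = 0.9 × 0.9 + 0.1 × x. The proportion among TCD-normal patients is the same, so the difference is 0.
- TCD positive in exactly the PD patients: predictive value = SPECT sensitivity in PD = 90%. Among TCD-normal patients the proportion abnormal is x, so the difference is 90% − x. No independence assumption is needed.

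| x (non-PD patients) | Unrelated TCD: predictive value | PD-exact TCD: predictive value | PD-exact TCD: abnormal SPECT if TCD normal | PD-exact TCD: difference |
|---|---|---|---|---|
| 0 (all normal) | 81.0% | 90% | 0% | 90 points |
| 0.38 (half APS at 76%, rest normal) | 84.8% | 90% | 38% | 52 points |
| 0.67 (all APS, low end) | 87.7% | 90% | 67% | 23 points |
| 0.76 (all APS, own data) | 88.6% | 90% | 76% | 14 points |
| 1.00 (all APS, high end) | 91.0% | 90% | 100% | −10 points |

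Up to x = 0.76, the predictive value separates the unrelated TCD from the PD-exact one by 90 − 88.6 = 1.4 to 90 − 81 = 9 points. At x = 1 the order reverses. The difference between TCD-positive and TCD-normal patients separates them by 14 to 90 points over the same span.

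**An imperfect but working TCD.** The article plans on 90% for TCD as well: "Assuming this 90% for TCD sensitivity we can accept as lowest border of the 95% confidence interval, 86% or higher". Assume further that TCD is positive in 25% to 50% of APS and 10% to 25% of other non-PD patients, and is independent of SPECT within a diagnosis.
- No APS, 25% of the others positive: 0.729 / (0.81 + 0.025) = 87.3%.
- No APS, 10% of the others positive: 0.729 / 0.82 = 88.9%. Among TCD-normal patients 0.081 / 0.18 = 45.0%, a difference of 44 points.
- All APS, 25% positive: (0.729 + 0.019) / 0.835 = 89.6%.
- All APS, 50% positive: (0.729 + 0.038) / 0.86 = 89.2%. Among TCD-normal patients (0.081 + 0.038) / 0.14 = 85.0%, a difference of 4 points.

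So a working TCD scores 87% to 90%, about 1 to 8 points above an unrelated one with the same case mix. The difference measure runs from 4 to 44 points.

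**PD share below 90% (assumed).** At 70% PD the unrelated TCD scores 63% (0.7 × 0.9) to 86% (0.63 + 0.3 × 0.76). At 50% it scores 45% to 83%. The PD-exact TCD stays at 90%.

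**Weight of MSA/PSP hits.** If all non-PD patients are APS and 25% to 50% are TCD-positive, such hits are 0.019 / 0.748 = 2.5% to 0.038 / 0.767 = 5.0% of all hits.

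**The case against.** The strongest reply is that this is one added sentence with no threshold or conclusion attached, and that the real TCD-SPECT comparison lies elsewhere. That stands. A reader might infer that the protocol compares the two tests by a predictive value alone. It does not: Methods, Data analysis and Discussion all judge both tests against the two-year diagnosis, with a full set of accuracy measures. A PD-type TCD in MSA or PSP counts against TCD in the planned PD-versus-APS analysis, and at 2.5% to 5% of hits it is not what drives the added measure.

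A reader might also infer that nearly every scan will be abnormal, or that a useless TCD would reproduce the pilot. Neither follows. On the planning figures 11% to 19% of scans are normal, and the upper end of abnormality needs every non-PD patient to be APS, although the inclusion criteria also admit essential tremor, vascular and drug-induced parkinsonism. If 95% were observed in about 191 TCD-positive patients (250 × 0.85 × 0.90; 181/191), the exact 95% interval would be 90.6% to 97.5%, which excludes 81% to 89%. Against that, even a PD-exact TCD is expected at 90%, so 95% is not the result that the planning figures predict.

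Nor do the documents show that the pilot's 95% was produced by its case mix. Without the counts, that share is unknown.

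Finally, it can be said that a condensed article leaves such tables to a fuller document. For the layout of a table that is fair. Here, however, the article names a specific measure, and the measure is a weak choice on the article's own inputs.

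**Conclusion.** The point holds for the additional TCD-SPECT analysis and no further. With 90% PD and 90% SPECT sensitivity, an uninformative TCD is expected to score 81% to 89% (91% at the top of the APS range), a working one 87% to 90%, and a PD-exact one 90%. The stated value alone barely separates them, and no comparison with the pilot's 95% can be interpreted without the overall rate of abnormal SPECT in both studies.

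The size rests on the 90% PD share, which is an expectation. With less PD the uninformative score is lower and the measure separates better, but the reader can know this only if the overall rate is reported. The range for a working TCD also rests on assumed TCD rates outside PD and on independence within diagnosis. The 90% for a PD-exact TCD needs neither. The main accuracy comparison is sound on this point, though it does not show how often SPECT is abnormal when TCD is normal.

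**What to change.** In Data analysis, replace the single predictive value with the TCD-by-SPECT 2x2 table. Give the proportion with abnormal SPECT among TCD-positive and among TCD-normal patients, each with a 95% confidence interval, their difference with its interval, and the overall proportion of abnormal SPECT beside them. State the number with an inconclusive TCD separately. Interpret the predictive value only next to the overall proportion, and do not set it against the pilot figure unless the pilot's overall rate is also shown.

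Show the same table by final diagnosis (PD, MSA/PSP, ET/VP/DIP), so that agreement in MSA and PSP is visible as such. This must stay descriptive: 250 × 0.85 × 0.10 gives about 21 assessable non-PD patients.

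All patients are to have both tests, so no new data are needed. The cost is one extra table and a less flattering headline figure. The TCD-normal group will also be small. With a PD-exact TCD it has about 21 patients, and a proportion of 38% then has a 95% half-width of 1.96 × √(0.38 × 0.62 / 21), or about 21 points. The imprecision should be stated with the result.
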